### 9.2.3 Assessment of other outcomes of interest

At BL socio-demographic data will be recorded to characterise the included patients (age, gender, activity level, and profession).

### 9.2.4 Assessment of safety outcomes

Any unexpected occurrences will be recorded to the case report form.

#### 9.2.4.1 Adverse events

Adverse events will be recorded to the CRF and transferred to a central documentation sheet.

#### 9.2.4.2 Laboratory parameters

Not applicable.

#### 9.2.4.3 Vital signs

Not applicable.

**9.2.5 Assessments in participants who prematurely stop the study**

Not applicable.

**9.3 Procedures at each visit**

Please refer to Table 3.

## **10. SAFETY**

### **10.1 Drug studies**

Not applicable.

### **10.2 Medical Device Category C studies**

Not applicable.

### **10.3 Medical Device Category A studies**

#### **10.3.1 Definition and Assessment of safety related events**

In our study an adverse event will be defined as any untoward medical occurrence in a subject without regard to the possibility of a causal relationship.

#### **10.3.2 Reporting of Safety related events**

Adverse events will be collected after the participant has provided consent and enrolled in the study. If a participant experiences an adverse event after the informed consent document is signed (entry) but he or she has not started to receive study intervention, the event will be reported as not related to study intervention. All adverse events occurring after entry into the study and until discharge will be recorded. An adverse event that meets the criteria for a serious adverse event (SAE) between study enrolment and discharge will be reported to the CEC as an SAE. If exercise is discontinued as a result of an adverse event, study personnel will document the circumstances and data leading to discontinuation of treatment.

A serious adverse event for this study is any untoward medical occurrence that is believed by the investigators to be causally related to exercise and results in any of the following: Life-threatening condition (that is, immediate risk of death); severe or permanent disability, prolonged hospitalization, or a significant hazard as determined by the treating therapists. Serious adverse events occurring after a participant is discontinued from the study will not be reported.

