| Therapies                         |                      |                      |                              | x                                       |                               |                       |
| Primary outcomes                  |                      | x                    | x                            |                                         | x                             | x                     |
| Secondary outcomes                |                      | x                    | x                            |                                         | x                             | x                     |
| Documentation of adverse events   |                      |                      | x                            | x                                       | x                             | x                     |

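### Section 10.3.2 makes causality part of seriousness, omits death and new hospital admission, and stops SAE reporting at discontinuation, which weakens safety reporting for serious, assessment-related and late events

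*Protocol*

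**What the plan says.** - **AE definition (10.3.1).** An AE is "any untoward medical occurrence in a subject without regard to the possibility of a causal relationship".
- **SAE definition (10.3.2).** The rule reads: "A serious adverse event for this study is any untoward medical occurrence that is believed by the investigators to be causally related to exercise". The event must also lead to one of the listed outcomes: "Life-threatening condition (that is, immediate risk of death); severe or permanent disability, prolonged hospitalization, or a significant hazard as determined by the treating therapists".
- **Events before training (10.3.2).** If a participant has consented but "he or she has not started to receive study intervention, the event will be reported as not related to study intervention".
- **Discontinuation (10.3.2).** "Serious adverse events occurring after a participant is discontinued from the study will not be reported".
- **Collection window.** Section 10.3.2 collects AEs from consent until discharge and sends SAEs in that period to the ethics committee. The row "Documentation of adverse events" in Table 1 is marked at T0, intervention, T1 and T2, and is blank at BL.
- **Objective and analysis.** Section 4.4 aims to record any AEs systematically so as to assess the safety of sensorimotor training. Section 11.4.5 promises an end-of-trial summary of the number and nature of all AEs.
- **Oversight.** Section 1.6 dispenses with a data safety monitoring committee. Section 11.4.5 leaves safety monitoring to the sponsor-investigator and the project leader.

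**The concern.** Seriousness describes what happened to the participant. Relatedness is a judgement about why. Section 10.3.1 keeps the two apart for AEs, and 10.3.2 joins them for SAEs. Once joined, the count of SAEs depends on the opinion of the people running the trial, and a grave event judged unrelated never reaches the outside body that could question that opinion. With no data safety monitoring committee, SAE reporting to the ethics committee is a main external check.

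The other rules in 10.3.2 point the same way: an incomplete outcome list, a fixed label for pre-training events, and a cut-off at discontinuation. Section 3.7 says no adverse events have been reported on the device since 1993. A trial that sets out to assess safety should be able to test that statement. An SAE count of zero produced under these rules would say little.

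**Working it through.** No figure in the plan needs reproducing. The check sets the rules side by side, counts the exposure involved, and follows four hypothetical events through the text.

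**1. Rules side by side**
- *Causality.* AE: any cause (10.3.1). SAE: only if believed related to exercise (10.3.2).
- *Outcome list.* Immediate risk of death counts, but death itself is not named. Prolonged hospitalisation counts, but a new admission is not named. Patients come from the outpatient department and public advertisement (6.1), so new admission is the form that hospital care would normally take. The remaining item, a significant hazard, is left to the treating therapists, who know the allocation (6.1, 6.3).
- *Discontinuation.* Section 7.4 makes injury after a fall or other trauma a ground for ending the measurement or intervention. Section 8.5 still invites withdrawn patients to the assessments, while 9.2.5, on participants who stop early, is marked not applicable. The visits at which late events could be found are foreseen, but the reporting rule excludes late SAEs.
- *Start of collection.* Consent (10.3.2) against T0 (Table 1).
- *End of collection.* Discharge, which is nowhere defined (10.3.2), against T2 (Table 1). T1 is in week 5 and T2 in week 9, so 9 − 5 = 4 weeks depend on what discharge means.

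**2. Device exposure before training**

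Section 9.2.2 sets five platform releases per measurement event, from a 5 cm deflection with all brakes released, at BL, T0, T1 and T2. Section 6.1 acknowledges that the assessment and the training share the device.
- *Participants at BL.* Section 11.2: 20 patients + 10 healthy = 30. Synopsis: 20 to 30 patients + 20 healthy = 40 to 50.
- *Releases at BL, where Table 1 has no AE mark.* 30 × 5 = 150 (11.2), or 40 × 5 = 200 to 50 × 5 = 250 (synopsis).
- *Per patient.* 4 events × 5 = 20 releases in all, of which 2 × 5 = 10 (BL and T0) precede the first session and fall under the automatic label.
- *Healthy participants.* They attend BL only and never start the intervention. Table 1 gives them no AE recording point, and the label applies to all their events.

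**3. Four hypothetical events**
- *Death during the training weeks, judged unrelated.* Recorded as an AE. Not an SAE, because the causality condition fails; death is not on the list either.
- *Fracture from a fall off the platform at BL.* Within 10.3.2 collection, but not prompted by Table 1. Labelled unrelated to the intervention. The protocol does not say whether the postural test counts as exercise for the SAE rule, so SAE reporting is doubtful.
- *Patient stops after an injury and has a new serious event two weeks later.* If the patient counts as discontinued from the study, the SAE is not reported, even if training is believed to be the cause. If only the training was stopped, it may be. The text does not settle which.
- *Event between T1 and T2.* Covered by Table 1. Covered by 10.3.2 only if discharge comes no earlier than T2.

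**The case against.** The strongest reply is that the safety objective rests on AEs, not on the SAE label. Section 10.3.1 ignores cause, 10.3.2 records every AE from consent until discharge, 9.2.4 puts unexpected occurrences on the case report form, 5.4 adds a weekly record, and 11.4.5 summarises everything. This stands. A reader might infer that the safety objective cannot be met, or that baseline falls and unrelated serious events would be absent from the report. The documents support neither. Such events remain AEs up to discharge, and what they lose is classification and reporting as SAEs. Consent precedes every study procedure (2.7), and 10.3.2 does not exclude healthy participants, so the blank at BL is a conflict between table and text. It does not show that baseline events go uncollected.

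Three further replies stand in part:
- An event before the first session cannot be due to training, so the automatic label is literally true of training. The gap is that no item captures relatedness to the assessments on the same device.
- Stopping exercise need not mean leaving the study, and 10.3.2 separately asks for the circumstances to be documented when exercise is stopped for an AE. But neither term is defined, and the heading of 7.4 speaks of discontinuing participants while its text ends a measurement or an intervention.
- Discharge might mean the end of participation at T2. It is an undefined term, not a proven contradiction.

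It is also fair that this is a small exploratory Category A trial with descriptive safety reporting, and that 2.5 promises annual safety reports to the ethics committee. Their content is not set out, and they do not restore an SAE classification that 10.3.2 withholds.

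**Conclusion.** The point holds as a defect in classification and reporting. Followed exactly, 10.3.2 keeps serious events judged unrelated from reaching the ethics committee as SAEs, names neither death nor new admission, and bars reporting of SAEs after discontinuation from the study. It also offers no way to attribute an event to the assessments. Table 1 conflicts with it at BL, and the four weeks from T1 to T2 depend on an undefined word.

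The reach is 30 to 50 participants and 150 to 250 platform releases at BL without an AE mark in Table 1, and half of each patient's 20 assessment releases under the automatic label. These are counts of exposure, not of expected events; the documents give no event rate. The counts assume that every planned participant completes the scheduled assessments. The effect of the discontinuation rule depends on whether stopping training counts as leaving the study.

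The safety objective is weakened for serious, assessment-related and late events, not defeated. No efficacy analysis is affected.

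**What to change.** 1. In 10.3.2, define seriousness by outcome only, and name death and hospital admission. Remove the causality condition from the definition.
2. Record relatedness as a separate item on the case report form, once for training and once for the assessments, in place of the automatic unrelated label.
3. State one collection window, from consent to T2 for patients and the single BL visit for healthy controls. Use it in place of discharge, and mark BL in the AE row of Table 1.
4. Delete the exclusion of SAEs after discontinuation. Distinguish stopping training from leaving the study, and collect events to the planned T2 in patients who stop training but still consent to follow-up. Bring 7.4, 8.5 and 9.2.5 into line with this. The grounds for stopping in 7.4 are not at issue here.

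The cost is protocol and case report form wording and a few more events to document. Sample size and outcome analyses are unchanged. Follow-up uses assessments to which 8.5 already invites withdrawn patients.

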## 11. STATISTICAL METHODS

### 11.1 Hypothesis

- |                            |                                                                                                                                                                                                                      |
|----------------------------|----------------------------------------------------------------------------------------------------------------------------------------------------------------------------------------------------------------------|
| 1° Null Hypothesis:        | Functional status and self-reported pain will reduce significantly in both groups, CG and EG, but no group interaction is expected.                                                                                  |
| 1° Alternative Hypothesis: | EG will show significantly more improvement in all primary and secondary outcomes as compared to CG.                                                                                                                 |
| 2° Null Hypothesis:        | Compared to healthy controls, patients with CNLBP will show no difference in postural control with optimal joint configuration variability when adjusting COM after destabilisation as compared to healthy controls. |
| 2° Alternative Hypothesis: | Patients with CNLBP will show different postural variability to adjust to destabilisation as compared to healthy controls.                                                                                           |
| 3° Null Hypothesis:        | Compared to healthy controls, patients with CNLBP will show no difference in cervical proprioception acuity as compared to healthy controls.                                                                         |
| 3° Alternative Hypothesis: | Patients with CNLBP will show reduced cervical proprioception acuity as compared to healthy controls.                                                                                                                |

### 11.2 Determination of Sample Size

This is the first study of its kind to investigate the effects of a sensorimotor training on dynamic postural control in patients with CNLBP and is therefore of explorative nature. Related to the primary hypothesis, however, a study using the same outcomes investigated the effects of treadmill training on gait in down-syndrome children and compared them to healthy subjects [29]. Although this is not a comparable study population it was used to estimate the power of the test. With a mean between-group difference of 1.4 and a pooled standard deviation of 0.19 the study revealed highly significant group effects ( $N=15$ ,  $p<0.01$ ).

Several studies have investigated the effects of sensorimotor training on pain and functional status. Two of the most recent ones [30, 31] have found significant time and group interactions using the same outcomes. Applying the results of these studies to a sample size calculation with an alpha value of 5% and the desired power 80%, it is expected that 10 patients per arm would suffice to reveal group differences and to detect change.

In terms of the secondary hypothesis, it must be referred to an article which used a similar motor task in an experimental setup with cross-sectional analysis of healthy participants. For the detection of within-subject difference of control parameters of the uncontrolled manifold approach, Scholz et al. [27] found that with a deflection of 0.06 m, the projections of joint configurations to the manifold differed significantly to the projection in the range space ( $N=9$ ,  $F_{1,8}=25.8$ ,  $p<0.001$ ). With a mean difference of 0.055 and a standard deviation of 0.015, this calculates to a power of  $>0.9$ .

Considering these findings and taking into account the explorative approach of this trial, a total number of 30 participants is planned (10 healthy subjects and 10 patients per intervention arm).

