| Number of Participants with Rationale: | 20 to 30 patients with low back pain (min. 10 per arm) and 20 healthy controls for the normative data. Based on previous studies with similar endpoints, the selected amount of participants has shown to suffice for an explorative approach with a desired power of 80% and an alpha of 0.05. |
| Study Duration:                        | September 2014 to December 2015                                                                                                                                                                                                                                                                 |
| Study Schedule:                        | Begin recruiting: January 2015
Last assessment: December 2015                                                                                                                                                                                                                                |
| Investigator and project leader:       | [name]
[contact]
[contact]                                                                                                                                                                                   |
| Study Centre:                          | Reha Rheinfelden
[name]

[name]                                                                                                                                                                                                                                   |
| Statistical Considerations:            | Student T-Test will be applied for group comparison at Baseline for cross-sectional comparison of LBP group with healthy group.

Repeated measure ANOVA with post-hoc analysis will be applied to test therapy effects.

Effect size will be calculated with Guyatt's effect size.  |
| GCP Statement:                         | This study will be conducted in compliance with the protocol, the current version of the Declaration of Helsinki, the ICH-GCP or ISO EN 14155 (as far as applicable) as well as all national legal and regulatory requirements.                                                                 |

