## **11.4 Planned Analyses**

Baseline imbalance between groups will be tested with a student t-test. Differences in means between healthy participants and patients with CNLBP will be analysed with independent student t-tests. A mixed (2) Group x (2) ME ANOVA with repeated measures during ME will be conducted for each dependent variable individually (Pain VAS, Functional Status ODI, Postural Control COM and CM, Proprioception JRE, and Motor Equivalence UCM).

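### The power above 0.9 in section 11.2 belongs to a within-subject contrast in 9 healthy people, not to the planned patient-versus-healthy comparison, and the healthy group is 10 in section 11.2 but 20 in the synopsis

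*Protocol*

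**What the plan says.** **Hypothesis and test.** The second alternative hypothesis in Protocol section 11.1 is that "Patients with CNLBP will show different postural variability to adjust to destabilisation as compared to healthy controls". The third makes the same comparison for cervical proprioception. Section 11.4 fixes the test: "Differences in means between healthy participants and patients with CNLBP will be analysed with independent student t-tests".

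**Power argument.** For the secondary hypothesis, section 11.2 turns to an article that used "a similar motor task in an experimental setup with cross-sectional analysis of healthy participants". The contrast taken from it is introduced by "For the detection of within-subject difference of control parameters of the uncontrolled manifold approach": projections on the manifold against projections in the range space, with N=9, F(1,8)=25.8 and p<0.001. The section then states "With a mean difference of 0.055 and a standard deviation of 0.015, this calculates to a power of" more than 0.9.

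**Numbers.** Section 11.2 concludes that "a total number of 30 participants is planned (10 healthy subjects and 10 patients per intervention arm"). The synopsis plans "20 to 30 patients with low back pain (min. 10 per arm) and 20 healthy controls for the normative data", "with a desired power of 80% and an alpha of 0.05".

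**The concern.** A power statement supports a hypothesis only if its effect size and standard deviation describe the contrast that will be tested. Here the source study has no patient group. Its mean difference compares two quantities measured in the same healthy person. The planned test compares means of two independent groups, and its power depends on a between-group difference and a between-person SD, neither of which the protocol gives.

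The three source figures (mean difference, SD and F) should also be linked by a simple identity, and as labelled they are not.

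Finally, the two places that state the sample size disagree on the healthy group. The comparison with healthy controls is one of the two main objectives in the synopsis. At stake are how many controls are recruited, and whether a reader takes the comparison to have a power that nobody has calculated.

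**Working it through.** **1. Reproducing the stated power.** Inputs from section 11.2: mean difference 0.055, SD 0.015, N=9. Alpha is 0.05 (synopsis), taken as two-sided because sidedness is not stated.

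- Paired standardised effect: dz = 0.055/0.015 = 3.67. Noncentral t power with n=9 is about 1.00.
- Starting from F instead: t = √25.8 = 5.08, dz = 5.08/√9 = 1.69, power 0.993.

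Both exceed 0.9, so the figure is correct for the within-subject contrast.

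**2. Do the inputs agree?** For a paired contrast, F(1, n−1) = n × (mean difference / SD of differences)².

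- SD of the differences 0.015: F = 9 × (0.055/0.015)² = 9 × 13.44 = 121. Allowing for rounding of both inputs, F lies between 111 and 132.
- A common per-condition SD of 0.015 with correlation r: SD of differences = 0.015 × √(2(1−r)). This gives F = 60.5 at r=0 and 30.25 at r=−1, the smallest possible value.
- 0.015 as the standard error of the difference: F = (0.055/0.015)² = 13.4.
- F=25.8 with a mean difference of 0.055 needs an SD of the differences of 0.055/1.69 = 0.0325.
- The stated p<0.001 agrees with F=25.8 (p = 0.00095).

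Two readings that the text does not state do come close:

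- 0.015 as the standard error of each condition mean, with correlation 0.74: 0.055² / (2 × 0.015² × 0.26) = 25.9.
- 0.015 as the SD of one projection, with 0.029 for the other and no correlation: 9 × 0.055² / (0.015² + 0.029²) = 25.5.

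**3. Group sizes.**

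| | Healthy | Patients | Total |
|---|---|---|---|
| Section 11.2 | 10 | 2 × 10 = 20 | 30 |
| Synopsis | 20 | 20 to 30 | 40 to 50 |

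The patient figures overlap at 20. The healthy figures do not.

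**4. What the planned test can detect.** Two-sample t-test, two-sided 0.05, df = n₁+n₂−2, noncentrality = d × √(n₁n₂/(n₁+n₂)). The values of d are assumptions, because the protocol gives no between-group effect.

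| Patients v healthy | d for 80% power | d for 90% power | Power at d=0.5 | d=0.8 | d=1.0 | d=1.2 |
|---|---|---|---|---|---|---|
| 20 v 10 (section 11.2) | 1.12 | 1.30 | 24% | 51% | 70% | 85% |
| 20 v 20 (synopsis minimum) | 0.91 | 1.05 | 34% | 69% | 87% | 96% |
| 30 v 20 (synopsis maximum) | 0.83 | 0.96 | 40% | 78% | 92% | 98% |

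**The case against.** **The basis is disclosed.** Section 11.2 says openly that the figure is a within-subject difference in healthy participants, and the only power attached to the planned sample is the desired 80%. That is fair, and it tempers the charge of a false claim. The figure is nevertheless offered for the secondary hypothesis, to which it does not apply.

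**The power is not miscalculated.** A reader might infer an arithmetic error in the 0.9. There is none: it follows from either set of inputs. The fault is relevance.

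**The conflict with F is not proof of a misreport.** A reader might conclude that 25.8 or 0.055/0.015 must be wrong. The F of 121 holds only if 0.015 is the SD of the differences, and 25.8 is also out of reach if it is a common per-condition SD. A standard error per mean with correlation about 0.74, or unequal SDs, comes close to 25.8. The source is not at hand. What stands is that the figures cannot be reconciled as labelled.

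**Low power is not shown.** A reader might infer that the comparison cannot reach 90%. That depends on the assumed effect: at d=1.0 with 30 against 20, power is 92%. The third alternative hypothesis is also directional, and a one-sided test would give 80% (20 v 20) and 86% (30 v 20) at d=0.8.

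**Recruitment has an end.** A reader might call the patient target contradictory or without a stop. The 20 patients in section 11.2 match the synopsis minimum, the synopsis dates the last assessment to December 2015, and section 11.3 reports results whatever sample size is reached by then.

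**The trial is explorative.** That excuses a small sample and the lack of a separate power for the third hypothesis. It does not excuse a power for another contrast or two sizes for one group.

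**Conclusion.** The point holds on three counts. The power above 0.9 does not bear on the planned patient-versus-healthy tests. The figures behind it cannot be reconciled as labelled (121 against 25.8), and the documents do not show which is at fault. The healthy group is 10 in one place and 20 in another, which moves the total from 30 to between 40 and 50.

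In size, the choice of section moves the detectable difference at 80% power from 1.12 to 0.91 or 0.83. Power at d=0.8 moves from 51% to 69% or 78%. These figures assume a two-sided 5% t-test with equal variances and no missing assessments, and the d of 0.8 is illustrative.

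This should be fixed rather than must be. The trial is explorative, no planned test changes, and the randomised comparison on VAS and ODI does not depend on this paragraph.

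**What to change.** 1. In section 11.2, remove the power above 0.9 as support for the patient-versus-healthy hypothesis, or state that it concerns a within-subject contrast and does not apply to the between-group test.
2. Check the mean difference, the SD and F against the cited article and say what the SD refers to, or drop all three.
3. State the same number of healthy controls and of patients in the synopsis and in section 11.2.
4. Give the detectable standardised difference for the chosen numbers (1.12, 0.91 or 0.83 at 80% power, two-sided 0.05) as the precision statement for the second and third hypotheses. Add that no between-group effect was available, so power at any given difference is an assumption.

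The cost is protocol wording and one look at the source article. A favourable figure is lost or qualified. No recruitment is needed beyond numbers already in the protocol.
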